### Screening and enrollment at sites

Using the same recruitment procedures used in preliminary studies (Suubi + Adherence R01HD074949), participants will be screened and recruited from 48 health clinics in six districts in Southern Uganda. Participants will be identified and recruited from the healthcare clinics associated with ICHAD, RTY-Uganda, and Masaka Diocese. Patients are seen at least annually and each patient on ART must have prescriptions filled monthly at the hospital/health clinic pharmacy [104]. Although appointment days (not times) are provided, most patients usually arrive early in the morning on days that are convenient for them and wait for several hours before they are seen. This provides an opportunity for recruitment through medical staff. The medical staff will create a list of all eligible families using medical records [104]. Each medical chart contains data on each patient’s HIV status and age, and family data. A clinic staff member will review the daily schedule of patients, and indicate to providers which patients are the eligible [104]. Providers will then present the project to caregivers of eligible adolescents during appointments. If caregivers are interested, verbal consent to be contacted by research staff (who will be on-site during clinics) will be requested [104]. After speaking with the research Project Coordinator about the study, interested caregivers will provide written consent for adolescent participation. Adolescents will be asked for written assent. If caregivers are not at the medical appointment, a community health worker from the clinic will outreach to parents and caregivers in the community. Given the cultural context within which the proposed study will be undertaken, if multiple adolescents in a family are eligible, all will be recruited if they meet the inclusion criteria [104]. This is intended to avoid any kind of envy or resentfulness that may occur when other adolescents in the family who meet the inclusion criteria were to be excluded [104].

### Contamination across conditions

Randomization to any one of the 16 conditions occurs at the level of the health clinic such that all adolescents from the same clinic receive the same intervention component to avoid contamination. The health clinics located in six districts in Southern Uganda are widely spread and far apart, in distance, from each other. Further, we will train all staff to encourage all families and participants to not discuss their intervention assignment to others if possible.

### Survey and clinical data collection

Survey assessments will occur at baseline, 6-, 12-, 24-, and 36-months, and all assessments will take place in ICHAD’s private research field offices in Masaka; at satellite sites (MildMay, RTY- Uganda); or at the participants’ homes (if they request it and there is sufficient privacy to ensure confidentiality, or at clinics (in a private room) with each lasting about 60 min [105]. Flexibility in interview location has been critical to Suubi + Adherence and other ICHAD studies success to date, with approximately 40% conducted in research offices in Masaka, and 50% in satellite sites [105]. Assessments are administered orally however for questions measuring sensitive behaviors, computer assisted self-interviews will be administered [106]. Non-sensitive questions will be interviewer-administered using Qualtrics [106]. Viral load assessments occur at the same time points but not at the 6-month follow-up assessment. Surveys will be conducted in English or Luganda depending on participants’ English proficiency [106]. All interviewers will be fluent in both languages. In Table 1, we provide a list of standardized instruments that will be included in the main statistical analyses. All measures used have been or will be pre-tested and made appropriate for the local Ugandan context [106].

**Table 1 Tab1:** Survey, clinical, and costs data

**Variables Moderators**	**Measurement**	**Time Point (Months)**
1. Demographics 2. Age 3. Sex (assigned at birth) 4. Family: Orphan status, socioeconomic status, family composition/structure, caregiver educational level 5. Geographic location and exposure to outside HIV-related programs	Self-reported Questionnaire	Baseline, 6, 12, 24, 36
**Mediators and Moderators**		
1. Financial literacy; 2. Financial management skills; 3. Engagement with financial institutions	Self-reported questionnaire Data from Bank Statements Self-reported questionnaire	6 months
1. Knowledge about ART 2. Internalized stigma 3. Sexual negotiation and communication skills 4. Mental health and HIV identity	Self-Report Questionnaire and Pill counts Social impact scale [107] Sexual Communication Scale [108] Condom negotiation scale [109] Beck Hopelessness Scale [110] and Center for Epidemiological Studies-Depression Scale (CESD) [111] & Negative Self-image sub scale of HIV Stigma Scale, [112] HIV-Positive Identity Questionnaire [113]	6 months
1. Problem solving of HIV care logistics 2. Self-esteem and social support 3. Engagement and retention in HIV care	Self-reported questionnaire Rosenberg Self-Esteem Scale [114] and Social Support Scale [115] HIV Index of Engagement [116, 117] and clinic records	6 months
**Primary Outcomes**		
Viral load		Baseline, 12, 24, 36
**Costs Data**		
Costs for staff time, supplies, overhead for IDAs	Project records, administrative review	(cost data will be collected during the 24 months that the intervention is delivered)

### Fidelity monitoring for interventions and quality assurance of study data

To ensure safety and protection of participants, we will conduct extensive research assistant (RA) training prior to study implementation. RAs employed in Uganda will have experience conducting interviews and data collection with vulnerable populations in Uganda. All will complete Human Subjects training as well as training on good clinical practice. Additionally, each of the RAs (to be hired) will be fluent in both English and Luganda, the local language that will be used in the study. RAs will have the ability to follow written and oral directions, be amenable to being evaluated, and have interpersonal flexibility. Research Assistant training (quantitative) will include (1) ethical issues in research; (2) establishing and maintaining rapport with participants; (3) obtaining informed consent; (4) addressing participants’ concerns with confidentiality and handling sensitive situations; (5) monitoring interviews; (6) obtaining accurate tracking information; (7) managing distress and conducting crisis and enhanced referrals; (8) detecting, handling, and reporting adverse events; and (9) working appropriately within host agencies/study sites. In addition, the performance of each RA (e.g., recruitment/refusal rates, data recording/entry errors) will be monitored; should an interviewer consistently perform at a level below other RAs for a 30-day period, he or she will be required to repeat the RA training.

Facilitator training will include (1) ethical issues in research; (2) establishing and maintaining rapport with participants; (3) addressing participants’ concerns with confidentiality and handling sensitive situations; (4) conducting their assigned intervention; (5) managing distress and conducting crisis and enhanced referrals; (6) detecting, handling, and reporting adverse events; and (7) working appropriately within host agencies/study sites. Intervention training will require pre-training preparation, asking RAs to review the protocol describing the goals, purpose, and design of the study, the theoretical framework, intervention manuals, materials, and a few key selected readings on theoretical concepts underpinning the intervention and to conduct mock sessions with trainers and peers. Facilitators will receive feedback from each other and the trainers and fashion common responses to issues that may arise during sessions. Facilitator training will stress the importance of implementation fidelity to study success. MPIs will certify facilitators prior to their study intervention facilitation. Certification requires satisfactory demonstration of key intervention activities and components.

For data management, the Management Information System for Individual Development Accounts Quality Control (MIS IDA QC) software [71] will be used to check for data-entry errors and prevent missing values. Frequency tables for all variables and measures of central tendency and variability for continuous variables will characterize the sample overall. Missing data will be addressed with direct maximum likelihood (ML) and multiple imputation (MI) [118] under the conditionally missing-at-random (MAR) mechanism [119]. Auxiliary variables will be included to help meet the MAR assumption [120, 121] and sensitivity analyses will be conducted with pattern-based MI [122] to assess the robustness of the MAR assumption [120, 123–127].

Secondary outcome, ART Adherence will be measured through self-report by three items: 1) frequency of pill taking, 2) ability to take pills, and 3) missed doses in the past 4-weeks and 6-months [128]. This will be augmented with a comprehensive unannounced pill count method that includes home visits, and ascertain each participant’s regimen before actual counting which would be done in the presence of the participant. Participants will be visited at an undisclosed time and day to count their pills once every 3 months throughout the study period.

### Follow-up plan and tracking

The project will take place in a highly stable region of Uganda where mobility is rare. We will collect telephone numbers, names, addresses, and contact information for three family/friends who know of each participant’s location. We will also be in contact with all participants regularly to determine enrollment and attendance. Moreover, we will have monthly contact with participants across the study conditions through the pill counting (see details above). These procedures will enable our team to continually engage all participants, and minimize loss to follow-up. These strategies were used in our earlier NIH funded studies [2, 53, 55, 56, 63, 65–67, 129–131] including the 6-year *Suubi* + *Adherence* study [104] which yielded a 93.4% retention rate over a 6-year period. Given these numbers and our team’s experience in the study region, we conservatively expect attrition by end of follow-up to be no more than 20%.

### Data sources

Data for the proposed study will be obtained through an eligibility screening checklist, and computer assisted, interviewer-administered structured questionnaires. Self-reported data via interviews will be collected at baseline and at all follow-up assessments from all participants. We will use self-report questionnaires with read-aloud procedures by professional trained staff to address issues of literacy. Multiple research assistants (RAs) will be hired to conduct assessments. To encourage truthful responding, we will remind participants that responses are confidential and explain to them the security system that makes it impossible to link a name to data. Each participant will complete a total of five interviews (one at baseline, then four follow-up interviews). One at 6 months (after delivery of intervention) then three 12 months apart (from intervention initiation).

The battery takes into account: 1) sensitivity to participant’s literacy (RAs read questions aloud and help fill out measures); 2) need for trust and rapport, and 3) use of local phrases and terms. In our previous work, participants completed these interviews without incident, often reporting positive experiences in being interviewed. Moreover, interview breaks and snacks will be provided and sensitive interviewers who are familiar with interview questions will facilitate the process.

### Harms

There are no major risks involved, however, a participant may feel embarrassed or uncomfortable during the consenting and interview process when answering sensitive and personal questions, taking blood for viral load testing. The process of blood draw may cause some discomfort, bleeding, or bruising where the needle enters the body, and in very rare cases, fainting or infection. First and foremost, interviewers will make it explicitly known to the participants that they may refuse to answer a question or decline to undergo a procedure, at any time. This will also be explained in writing on the consent forms. If a participant tells the interviewer that he/she is uncomfortable with a particular topic, that he/she prefers not to discuss a particular topic or feels he/she cannot participate in the biomarker process, the interviewer will move on to the next question/part of the interview.

### Data analysis plans

Effect coding is used to produce uncorrelated main effect estimates, unbiased standard errors, and clearer interpretations of interactions between components in factorial designs. The single covariate of randomization stratum with four levels reflecting the combination of two binary variables: 1) ALHIV population size (medium size vs. large) and 2) geographical location (rural vs. urban), to ensure balance on those variables. Our preliminary analysis will focus on assessing balance in assignment to conditions. The stratified restricted cluster randomization is expected to produce balance across the 16 conditions [132]. We expect to have equal cell sizes to estimate the main effects and interactions and equal percentages of ALHIV population sizes and geographical locations in our main comparisons. For thoroughness, we will check for imbalances across the four component comparisons (e.g., percent of rural vs. urban participants in the financial literacy versus no peer financial literacy comparison), rather than across 16 conditions because recall that a 2^4^ factorial design is not a 16-arm comparison. In the unlikely event that an imbalance does occur by ALHIV population size and/or geographic location, we will use propensity score matching (i.e., a conditional probability of having one component delivered versus another) with baseline covariates collected in our survey to estimate the primary outcome under the counterfactual assumption of balanced groups [133–135]. The proposed analyses and syntax code will be documented and made available on request to enable review, transparency, and results reproducibility.

The goal is estimating main effects for sustained viral suppression. Factorial designs with continuous, normally-distributed outcomes measured cross-sectionally are often evaluated using an Analysis of Variance (ANOVA), which is a special case of a general linear model (GLM). For.analyses with clustering (within-subject correlations) and non-normal outcomes (e.g., sustained viral suppression), generalized estimating equations (GEE) can be used instead of ANOVA [136–138]. Recall that our primary outcome is a single computed variable of sustained viral suppression—all 1 s on the Y variable at 12-, 24-, and 36-month follow-up assessments. Thus, we are using GEE, not based on repeated measures across time, but because of clustering that will occur through the cluster randomized trial (CRT) design approach we are using. Participants who visit the same clinic may not be statistically independent [137]. Thus, GEE can properly account for the correlation of participants within the same clinic by using robust standard errors to correct inferences, even if the chosen correlation structure remains slightly misspecified. Moreover, within-clinic correlations of outcomes are considered nuisance parameters, not quantities of interest to be modeled explicitly [136]. In GEE, we will a priori specify a working correlation structure—specifically the exchangeable correlation structure (compound symmetry assumption)—given the assumption of a balanced factorial design and a single level of clustering by clinic [139]. Alpha (α) will be set at 0.05 for estimating main effects, which are orthogonal (i.e., independent) of each other. As detailed by Kahan and Morris [140], stratification during the randomization process must be accounted for in the primary analysis as it may lead to correlations among the participants in each cell. Uncorrected, this would bias standard errors estimates, producing wider confidence intervals, a lower Type I error rate, and affect statistical power. Thus, all analyses will be adjusted by randomization stratum to produce unbiased estimates.

Factorial designs are innovative in their ability to estimate how two or more components interact, which is not possible with a multi-component packaged intervention. Following the MOST framework, α will be set to 0.10 for all interaction effects, which is justified by the decision-priority perspective [141] guiding this study. To enhance rigor, we will test if interactions among components yield additive and/or synergistic interactions. Additional exploratory analyses will add sex as a covariate and extend each of the previously-described analyses to include interactions of each effect with sex. We propose the following hypotheses for the mediation analyses (also depicted in conceptual model, Fig. 2).

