### Primary outcomes

We are measuring sustained viral suppression, which is a measure of viral load constancy.that is of great clinical and public health importance. Sustained viral suppression is defined as confirmed viral load laboratory tests of < 1000 copies per mL on all 12-, 24-, and 36-month follow-up assessments. Participants who have a viral load laboratory tests of > 1000 copies per mL at any follow-up assessment will be treated as not having sustained viral suppression. In line with another factorial experiment for viral suppression, missing viral load data and deaths will be treated as non-suppression and failure (details below). Participants who are virally suppressed on all 12-, 24-, and 36-month follow-up assessment are coded as 1 for sustained viral suppression. Participants who have missing data or are not virally suppressed on one or more 12-, 24-, or 36-month follow up assessment are coded as 0 for not sustained viral suppression. This handling of missing outcome data allows for calculating the differences in proportions between those who did and did not sustain viral suppression using an intent-to-treat approach [73, 103].

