### Eligibility

A total of 576 ALHIV (aged 11–17 years) will be recruited from 48 health clinics. Adolescents’ inclusion criteria are: 1) An adolescent living with HIV (confirmed by medical report and aware of status); 2) living within a family; 3) being 11–17 years of age (at enrollment); 4) Prescribed ART; and 5) enrolled in ART care at one of the 48 health clinics in the study districts. Health clinics would be eligible if they: 1) have existing procedures tailored to adolescent adherence (including adolescent-specific clinic days and peer counselling) and 2) accredited by the Uganda Ministry of Health as a provider of ART within the study districts. Exclusion criteria include an adolescent’s inability to understand study procedures and participant rights as assessed during informed consent/assent process with the adolescent or parent. If the adolescent or adult caregiver presents with emergency needs (e.g., hospitalization), needed care will be secured, rather than study participation.

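### The primary GEE adjusts for randomization stratum alone and leaves out baseline viral suppression, giving up precision and protection against chance imbalance that data already scheduled could supply

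*Protocol article*

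**What the plan says.** All references are to the protocol article.

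- **Covariates.** Data analysis plans describes "The single covariate of randomization stratum with four levels reflecting the combination of two binary variables", the two variables being the size of the clinic's ALHIV population and rural or urban location. The same section adds that "all analyses will be adjusted by randomization stratum to produce unbiased estimates". The only further covariate named for the component effects is sex, in exploratory models.
- **Baseline viral load.** Table 1 lists viral load at "Baseline, 12, 24, 36" months. Survey and clinical data collection lists surveys from baseline to 36 months and adds: "Viral load assessments occur at the same time points but not at the 6-month follow-up assessment".
- **Who enters.** The treatment-related criteria under Eligibility are "4) Prescribed ART; and 5) enrolled in ART care at one of the 48 health clinics in the study districts". There is no viral-load criterion, so suppressed and viraemic adolescents can both enrol.
- **Outcome.** "Sustained viral suppression is defined as confirmed viral load laboratory tests of < 1000 copies per mL on all 12-, 24-, and 36-month follow-up assessments". In addition, "missing viral load data and deaths will be treated as non-suppression and failure".
- **Fallback.** Propensity score matching on baseline survey covariates is planned, but only if population size or location turns out imbalanced.

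**The concern.** The outcome asks whether a participant stays under a threshold at three later visits. Whether the participant was under it at enrolment is a natural predictor, and that measurement is already scheduled. It does not appear in the strata, the balance check, the primary GEE, the exploratory covariates or the moderators named in the text. The covariate set is stated positively as a single variable, so this is a choice and not merely a detail left for later.

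The fallback does not fill the gap. It is triggered only by the two stratification variables, which the design already balances, and it draws on survey covariates, whereas viral load is a laboratory measure. A chance imbalance in baseline suppression would neither be looked for nor acted on.

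At stake is the precision of each component contrast. These contrasts feed the choice of components, and Determining the Optimized Intervention gives as its example a difference of 5% in odds. In the mediation analysis there is a second reason: the path from the 6-month mediator to 12-month suppression is not randomised, and baseline suppression could plausibly affect both ends of it.

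**Working it through.** **Inputs from Power analysis.** Base rate 50%, ICC 0.024, N = 480 in 48 clinics (10 per clinic), α = 0.05 (two-sided assumed), power 80%, detectable odds ratio 1.77 or 14 points. With equal cells each main effect compares 24 with 24 clinics.

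**1. Reproducing the plan's figure.** Design effect = 1 + (10 − 1) × 0.024 = 1.216. Effective n per level = 240 / 1.216 = 197.4. An odds ratio of 1.77 from 50% gives p2 = 1.77 / 2.77 = 0.639, a difference d = 0.139. With pooled variance, power = Φ{[d√n − 1.96√(2p̄q̄)] / √(p1q1 + p2q2)} = Φ[(1.953 − 1.372) / 0.693] = Φ(0.84) = 0.80. The stated figure reproduces without any baseline covariate.

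**2. Adding baseline suppression.** The documents give neither the baseline suppression rate nor its association with the outcome, so both are assumed. With baseline rate s and sustained suppression pa (suppressed at baseline) and pb (not suppressed), averaging p = 0.50:

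R² = φ² = s(1 − s)(pa − pb)² / [p(1 − p)], and effective n = 197.4 / (1 − R²).

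For s = 0.65:

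| pa vs pb | φ | R² | Effective n | Detectable difference | Marginal OR | Power at OR 1.77 |
|---|---|---|---|---|---|---|
| no covariate | – | – | 197.4 | 13.9 points | 1.77 | 80% |
| 55.0% vs 40.7% | 0.14 | 0.019 | 201.2 | 13.8 | 1.76 | 81% |
| 60.0% vs 31.4% | 0.27 | 0.074 | 213.2 | 13.4 | 1.73 | 83% |
| 65.0% vs 22.1% | 0.41 | 0.167 | 237.0 | 12.7 | 1.68 | 87% |
| 70.0% vs 12.9% | 0.55 | 0.297 | 280.8 | 11.7 | 1.61 | 92% |

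With s = 0.75 the picture is similar: 60% vs 20% gives R² = 0.12 and power of 85%. If all 576 are analysed, as missing-as-failure implies, power at OR 1.77 is 85% unadjusted and 86% to 95% over the four rows.

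**3. Effect of missing-as-failure.** If 20% are lost regardless of baseline status and coded 0, the overall rates are 0.8 times those in completers. The last row then needs 70 / 0.8 = 87.5% vs 12.9 / 0.8 = 16.1% among completers, and the third row 81.3% vs 27.6%. The upper end therefore requires a strong association.

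**4. Simulation check.** GEE, 48 clinics of 10, exchangeable correlation, bias-reduced standard errors, 400 replicates. Power went from 0.645 to 0.693 (φ 0.27) and from 0.66 to 0.82 (φ 0.55). Type I error was 0.04 to 0.05 without the covariate and 0.04 with it. The small-sample standard error lowers absolute power; only the gain is used here. The Monte Carlo standard error is about 0.024 for power.

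**5. Chance imbalance.** With 288 vs 288 participants, s = 0.65 and an ICC of 0.024 borrowed from the outcome, the design effect is 1 + 11 × 0.024 = 1.264. The SD of the difference in baseline suppression is √(2 × 0.2275 × 1.264 / 288) = 4.5 points, a 95% range of about ±8.8 points. Multiplying 8.8 by (pa − pb) gives possible shifts in the unadjusted contrast of 1.3 points (φ 0.14), 3.8 points (φ 0.41) and 5.0 points (φ 0.55), against a 14-point target.

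**The case against.** The strongest reply is that nothing here is an error. A stratum-adjusted GEE with robust standard errors is valid under clinic randomization, and the plan reaches its own 80% power without the covariate. **This stands.** A reader might infer that an uncorrected imbalance biases the component effects. The documents do not support that: chance imbalance is ordinary sampling error, and the confidence interval already covers it. The contrast's standard error is about 14 / 2.8 = 5 points, and the shifts in step 5 are part of that, not added to it.

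Second, the size is wholly assumed. A reader might take baseline status to be the strongest predictor and expect power of 85% or more. The documents contain no association to support either, and at φ 0.14 the gain is about one percentage point. **This stands**, and is why the whole range is shown.

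Third, adjustment turns the odds ratio into a conditional one and does not generally shrink the standard error of its logarithm. **This stands.** The gain is in the power of the test and in the precision of a standardised marginal effect.

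Fourth, baseline viral load may not exist for everyone, because Harms lets participants decline a procedure. **This stands**, and the fix needs a rule for it.

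Fifth, the covariate sentence is incomplete, and stating that analyses adjust for stratum does not say they adjust for nothing else. Figure 2 and any SAP are not shown. **This stands only in part:** the text calls stratum the single covariate, which is hard to read as leaving room for another.

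**Conclusion.** The point holds as one of efficiency. The plan fixes a covariate set that omits a scheduled baseline measurement of the same quantity as the outcome. The cost is lost precision and lost protection against chance imbalance between 24 and 24 clinics. It is not bias, and the type I error is not in question.

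For an assumed φ of 0.14 to 0.55, power at the effect now detectable with 80% power would be about 81% to 92%, and the detectable difference would fall from 13.9 points to between 13.8 and 11.7. Missing-as-failure coding pulls toward the lower end. The range assumes 65% suppressed at baseline, N = 480 and the plan's ICC. In the mediation models the omission is potentially one of confounding, because the mediator-outcome path is not randomised; the documents give no figure from which to size it.

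**What to change.** Before outcome data are analysed:

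- Pre-specify baseline suppression (below 1000 copies per mL, yes/no) as a covariate with stratum in the primary GEE, and in the 12-month and mediation models.
- State how missing baseline values are handled, by a missing-indicator category or single imputation, so that no participant is dropped and the intent-to-treat set stays whole.
- Report a standardised marginal risk difference (or marginal odds ratio) with cluster-robust inference beside the conditional odds ratio.
- Keep the stratum-only model as a sensitivity analysis.

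The cost is a short change of wording and somewhat more analysis work, chiefly the standardisation. No new data are needed. The downside is that the conditional odds ratio is not directly comparable with the planned 1.77; the marginal estimate covers that comparison.

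### The propensity-matching fallback targets an imbalance that the primary model already adjusts for, and would undo the balanced factorial design

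*Protocol article*

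**What the plan says.** All of this stands in the protocol article under Data analysis plans.

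- **The covariate.** The model carries one: "The single covariate of randomization stratum with four levels reflecting the combination of two binary variables", namely ALHIV population size (medium or large) and location (rural or urban). Later the section adds that "all analyses will be adjusted by randomization stratum to produce unbiased estimates".
- **The expected balance.** "The stratified restricted cluster randomization is expected to produce balance across the 16 conditions", and "We expect to have equal cell sizes to estimate the main effects and interactions". The balance check itself is made for each of the four component comparisons, not across the 16 conditions.
- **The fallback.** "In the unlikely event that an imbalance does occur by ALHIV population size and/or geographic location", the response is that "we will use propensity score matching (i.e., a conditional probability of having one component delivered versus another) with baseline covariates collected in our survey", and its purpose is "to estimate the primary outcome under the counterfactual assumption of balanced groups".

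The same section relies on effect coding for uncorrelated main effects, and chooses the exchangeable GEE on the assumption of a balanced factorial with one level of clustering. Under Randomization, clinics are the randomised unit. Under Primary outcomes, missing viral loads and deaths count as failures so that the analysis follows intent to treat.

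**The concern.** The fallback is aimed at the primary outcome and is not labelled a sensitivity analysis. It raises two problems.

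First, the variables that set it off are exactly the two that make up the stratum covariate. If the model already conditions on stratum, an uneven split of strata between the levels of a component is dealt with, and matching can remove nothing more from that source.

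Second, matching suits this design poorly. The propensity is defined for one component at a time, while there are four crossed components, and it is built from participants' survey answers, while allocation was by clinic. Taken as written, it yields up to four different matched samples. In general these will have unequal cells and correlated components, and no single sample is left for the interaction tests that belong to Aim 1. Dropping unmatched participants also sits badly with the intent-to-treat approach under Primary outcomes.

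**Working it through.** **1. Overlap of trigger and covariate.** Trigger: population size and/or location. Stratum covariate: population size × location. They are the same two variables. The matching set is the survey covariates. Table 1 (Survey and clinical data collection) lists geographic location but not ALHIV population size, so matching may omit one of the variables that triggered it.

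**2. Reproducing the planned figure.** Inputs from Power analysis: N = 480, 48 clinics (10 per clinic), ICC 0.024, base rate 50%, α = 0.05 (two-sided assumed), power 0.80.
- Design effect = 1 + (10 − 1) × 0.024 = 1.216.
- Effective n per level of a component = 240 / 1.216 = 197.4.
- Solving the pooled two-proportion formula for 80% power gives OR 1.772, a difference of 13.9 points and a standardised effect of 0.282. The article states 1.77, 14% and 0.28, so its figure reproduces.

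**3. Power if matching drops participants.** OR 1.77 on a 50% base is 1.77 / 2.77 = 63.9%. The losses are illustrative and assumed to be spread evenly over clinics.

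| Kept | Per clinic | Design effect | Effective n per level | Power, pooled | Power, unpooled |
|---|---|---|---|---|---|
| 480 | 10 | 1.216 | 197.4 | 79.9% | 80.4% |
| 432 (−10%) | 9 | 1 + 8 × 0.024 = 1.192 | 216 / 1.192 = 181.2 | 76.4% | 77.0% |
| 360 (−25%) | 7.5 | 1 + 6.5 × 0.024 = 1.156 | 180 / 1.156 = 155.7 | 69.9% | 70.6% |

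**4. Simulation of matching on one component.** Settings, all assumed because the article gives none: 48 clinics, 3 per condition, 10 participants each, ICC 0.024, no component effect, a location effect of 0.5 on the log-odds scale, 1:1 matching without replacement, caliper 0.2 SD of the logit, 800 runs per scenario.

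| Rural clinics, on/off | Matched on | Kept of 480 | Mean smallest–largest cell | Mean largest correlation between components | Bias, stratum-adjusted / matched |
|---|---|---|---|---|---|
| 13/11 | strata only | 440 | 16.8–30.0 | 0.063 | −0.002 / −0.001 |
| 13/11 | strata + 6 covariates | 407 | 20.6–29.2 | 0.043 | 0.000 / 0.003 |
| 14/10 | strata only | 400 | 8.6–30.0 | 0.111 | −0.007 / −0.008 |
| 14/10 | strata + 6 covariates | 391 | 18.8–29.1 | 0.053 | 0.000 / 0.004 |

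Before matching, every cell holds 480 / 16 = 30 participants and the components are uncorrelated. The stratum-adjusted model on all participants is already essentially unbiased, and matching gains nothing on that score. Its empirical standard error was 0.5% to 7% larger, with simulation error of about 2.5% on each standard error.

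**5. Balance across 16 conditions.** 48 / 16 = 3 clinics per condition, and there are four strata, so no condition can contain all four. The component margins are another matter: 48 / 2 = 24 against 24 clinics. Assuming four strata of 12 clinics (the sizes are not given), an allocation exists with exactly 3 clinics per condition and a 6/6 split of every component in every stratum. Each stratum takes one balanced half-fraction (8 conditions) plus one balanced quarter-fraction (4 conditions).

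**The case against.** The strongest reply is that this is a contingency the authors call unlikely, triggered by baseline variables, with a modest effect if it is ever used. Most of that stands.

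- **Likelihood.** A reader might infer from 3 clinics and four strata that the trigger is bound to fire. The documents do not support this. Balance is checked at the four component comparisons, where exact balance can be achieved, and the randomization is stratified and restricted.
- **Type I error.** A reader might infer that a data-dependent switch inflates it. The trigger is clinic size and location, not the outcome. The problem is a changed sample and estimator, not a demonstrated inflation.
- **Duplication.** The adjustment overlaps with the stratum covariate but is not identical to it, because matching would also use other survey covariates. Balancing those is a legitimate aim, but covariate adjustment in the same model can pursue it without discarding anyone.
- **Missing details.** The imbalance threshold, caliper and matching ratio may stand in a fuller document, and their absence is not the complaint.
- **Implementation.** The text does not say that the GEE is abandoned or that participants are dropped. A GEE could be fitted to a matched sample, and how much is lost depends on the method. Still, matching commonly discards unmatched participants, and a one-component propensity does not yield one sample that serves four components.

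**Conclusion.** The point holds as a stated rule that would make the primary analysis worse, not as a missing detail. With stratum in every model, the fallback cannot improve on the imbalance it is meant to cure, and its likely side effects are lost participants, component-specific samples, unequal cells and correlated effects.

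The size is modest. Losses of 10% and 25% of 480 bring power at OR 1.77 to about 76–77% and 70–71%. The simulated losses ran from 40 to 89 participants (8% to 19%), so the 25% case lies beyond them. These figures rest on assumed matching settings. Because missing outcomes count as failures, the number analysed could also be nearer 576 than 480, which would make the loss of power smaller. The change is worth making because it is clear and nearly free, not because the trial is at serious risk without it.

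**What to change.** Delete the propensity-matching sentence. State that the stratum-adjusted GEE on all randomised participants is the primary analysis whatever balance is observed, and that any further adjustment for survey covariates is a sensitivity analysis in that same model, on the same participants. This removes work and costs one edited sentence plus one added.

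In the same edit, correct the sentence that expects balance across the 16 conditions so that it refers to the component comparisons of 24 against 24 clinics; the section already expects equal percentages there.

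Separately and optionally, baseline viral suppression, which the trial already collects, could be a pre-specified covariate to gain precision. That is not needed to resolve this point and would change the present single-covariate specification.
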